#### Intervention pilot study

A pilot study was conducted with 154 Brazilian adolescents to assess *Topity’s* user experience (e.g., ease of use) and acceptability (e.g., enjoyment; content relevance) prior to the main trial. Participants were 13–18-year-old girls and boys (56% girls; *M* = 15.67, SD = 1.62) from geographically diverse regions of Brazil, who were recruited via peer-support leaders, secondary school teachers and non-profit organisation officers known to UNICEF. Following parental consent and participant assent, adolescents were invited to engage with *Topity* as much as they needed over a one-week period. Adolescents assessed the chatbot on 11 acceptability factors, using 7-point response scales (e.g., 1 = *not at all interesting*; 7 = *very interesting*). Factors included: emotive response to the chatbot (e.g., enjoyment, interest, comfortability), relevance (e.g., pertinence, importance and helpfulness of the content to the user and other young people in Brazil), ease of use (e.g., speed and accuracy of responses) and willingness to recommend (e.g., how likely the user would recommend *Topity* to a friend and re-engage in the future). Mean scores for each item, as well as an overall acceptability score are provided in the supplementary materials. Overall, *Topity* was rated highly on overall user experience and acceptability across genders (girls; *M* = 6.40, *SD* = .65; boys; *M* = 6.0, *SD* = 1.03) and age (13–15 years; *M* = 6.41, *SD* = .61; 16–18 years, *M* = 6.07, *SD* = .99). Based on this feedback, no modifications were made to the chatbot prior to the main trial.

### Measures

Research measures are presented in Table 3. One measure was purpose-built for the current research (i.e., body image self-efficacy). Acceptability and adherence measures were informed by existing reviews [52, 53], with remaining measures validated for use among adolescents.

**Table 3 Tab3:** Research outcomes and internal consistencies

*Demographics*	Age, gender identity, ethnicity, race, state and region of residence	T1
*Primary outcomes*		
State body satisfaction	A single 11-point scale assessing the immediate impact of a chatbot technique on participants’ state body satisfaction (*How satisfied are you with your appearance, right now, in this moment?*). Total score range 0 (*not at all*) to 10 (*very much*). Higher scores reflect greater satisfaction.	Start of chatbot experience. Post-intervention technique. 12-, 16-, 23.5-h after non-engagement.
Trait body satisfaction	Body Esteem Scale for Adolescents & Adults in Brazil [46, 47]. Appearance Positive (AP; e.g., *I like how I look like in photos*), Appearance Negative (AN; e.g., *I feel ashamed about my appearance*) and Weight (e.g., *I am satisfied with my weight*). Mean subscale scores range between 0 (*never*) and 5 (*always*). Higher scores reflect higher esteem. Internal consistency: AP = .85; AN = .88; Weight = .89.	T1- T4
*Secondary outcomes*		
State affect	A single 11-point scale assessing the immediate impact of a chatbot technique on participants’ state affect (*How happy are you, right now, in this moment?*). Total score range between 0 (*not at all*) to 10 (*very much*). Higher scores reflect greater positive affect.	Start of chatbot experience. Post intervention technique. 12-, 16-, 23.5-h after non-engagement.
Trait affect	The Positive and Negative Affect Scale for Children 8-item; PANAS-C8 [48] 8-items related to emotive states (4 positive [e.g., *joyful*]; 4 negative [e.g., *irritated*]). Positive and negative affect subscale scores range between 1 (*not at all*) and 5 (*extremely*). Higher scores reflect greater positive or negative affect. Internal consistency: PA = .77; NA = .76	T1 - T4
Trait body image self- efficacy	A purpose-built measure, The Body Image Self-Efficacy Scale, derived from existing self-efficacy measures [49–51]. 5 visual analogue scales (VAS; 0 [*not at all confiden*t] to 100 [*very confident*]) assessing participants’ belief in their ability to execute strategies to improve their body image (e.g., *I am able to learn and practice new skills to help improve my body image*). Total mean scores range between 0 and 100. Higher scores reflect greater body image self-efficacy. Internal consistency: .82	T1 - T4
Intervention adherence	Digital metrics will assess participants engagement with the chatbot, including: • Percentage of participants who complete the intervention (e.g., minimum of 1 technique completed over the 72-h intervention period); • Percentage of participants who enter the intervention but do not complete the intervention; • Percentage of participants who complete each intervention technique; • Average number of techniques completed; • Average length of time taken to complete each technique; • Average length of time spent engaging with the chatbot over the 72-h period.	72-Hour Intervention Period
Intervention acceptability	11 items assessed participants acceptability of the chatbot. Factors included: • Emotive response to the chatbot (e.g., enjoyment, interest, comfortability); • Relevance (e.g., pertinence, importance and helpfulness of the content to the user and other young people in Brazil); • Ease of use (e.g., speed and accuracy of responses); and • Willingness to recommend (e.g., how likely the user would recommend Topity to a friend and re-engage in the future). Item scores range between 1 (e.g., *not at all enjoyable*) and 7 (e.g., *very enjoyable*). Higher scores reflect greater acceptability.	T4

Note. T1 = Baseline; T1 = Baseline; T2 = Post-intervention; T3 = One-Week Follow-Up; T4 = One-Month Follow-up

### Participant recruitment and procedure

A community sample of 2800 adolescents aged 13–18 from diverse ethnic, geographic and socio-economic backgrounds will be recruited via a Brazilian research agency’s recruitment panels (i.e., via email to their participant databases) and via UNICEF’s online communication platforms (e.g., U-Report^1^). Recruitment will occur 2 weeks prior to the trial commencing. Given UNICEF’s reach and expertise with underserved adolescents in Brazil, the inclusion of this recruitment channel will ensure that a diverse sample is approached for participation. Further, recruitment numbers across these metrics (e.g., geography) will be regularly monitored and addressed by the research team to ensure diversity across the sample is achieved. Recruitment materials will include a link to an online screener questionnaire to determine participant eligibility. After being screened as eligible, participants will be emailed an information pack to be read with their parent or guardian. Parents will provide consent as per the Brazilian General Data Protection Law, by uploading their signature to online identification verification software that is monitored by the research agency. Following parental consent, adolescents will complete the online self-report assessment (T1), which will commence with adolescents providing informed assent. Those who do no assent will not proceed with the trial. On completion of the survey, adolescents will be randomised into one of two conditions: intervention or assessment-only. Those in the intervention condition will receive a link to the chatbot 24-hours after completing the baseline assessment. Those in the assessment-only condition will be provided with a link to the chatbot after they have completed all assessment timepoints.

Adolescents in the intervention condition will be encouraged to engage with the chatbot as much as possible over a 72-hour period. During this time, participants may complete the eight intervention techniques as many times as they like. Participants will be assessed on state body satisfaction and affect when they first enter the chatbot and immediately after engaging with a technique. If participants do not engage with the chatbot after 12-, 16 and 23.5 hours, they will receive a prompting notification that encourages engagement with the chatbot. That is, if they do not engage after the 12-hour prompt, they will receive up to two more prompts.

At completion of the 72-hour intervention period, both conditions will be assessed on primary and secondary trait outcomes immediately post-intervention and, at one-week and one-month follow-up. Those in the intervention condition will be encouraged to continue using the chatbot. Following the one-month follow-up assessment, all participants will be debriefed on study aims and objectives, and provided with mental health resources accessible in Brazil. Assessment-only participants will be invited to engage with the chatbot; however, their engagement will not be monitored or assessed. Lastly, to compensate participants for their data usage, they will receive an electronic voucher to the value of R$100 and R$80, for the intervention and control condition, respectively. Participants were not notified of the compensation value until study completion. 

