**Methods:**

A two-armed fully remote randomised controlled trial will evaluate the chatbot’s effectiveness at improving body image and well-being. Adolescent girls and boys (*N* = 2800) aged 13–18 years recruited online will be randomly allocated (1:1) into either: 1) a body image chatbot or 2) an assessment-only control condition. Adolescents will engage with the chatbot over a 72-hour period on *Facebook Messenger*. Primary outcomes will assess the immediate and short-term impact of the chatbot on state- and trait-based body image, respectively. Secondary outcomes will include state- and trait-based affect, trait self-efficacy and treatment adherence.

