### The current trial design

This paper outlines the protocol for the co-creation and controlled evaluation of a chatbot targeting risk and protective factors for body image concerns among Brazilian adolescents. A two-arm fully remote randomised controlled trial (Fig. 1) will compare a chatbot intervention to an assessment-only control condition. Participants in the intervention condition will interact with the chatbot over a 72-h period, while participants in the control condition will receive ‘standard care’ for body image concerns among adolescents in Brazil, which at present is no intervention. This protocol paper and the randomised controlled trial design were guided by the Standard Protocol Items: Recommendations for Interventional Trials (SPIRIT; see Fig. 2 and supplementary materials) and the Consolidated Standards of Reporting Trials (CONSORT [28];), including the extension for Electronic Health (CONSORT - EHEALTH [29] see supplementary guidelines).

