**Fig. 2 Fig2:**
[figure not shown]
Schedule of enrolment, interventions, and assessments according to the SPIRIT guidelines

Assessment of primary and secondary trait outcomes will be conducted at baseline (T1), post-intervention (i.e., 3 days; T2), one-week (T3) and one-month follow-up (T4). Participants in the intervention condition will also be assessed on state-based body satisfaction and affect immediately after engaging with each technique. To our knowledge, this is the first chatbot to target body image among Brazilian adolescents. Therefore, a secondary aim is to assess users’ engagement and adherence. Hypotheses were formulated for overall chatbot efficacy (H1-H2), moderation effects within sub-samples (H3), and intervention engagement and adherence (H4):
**H1:** The chatbot was designed to provide immediate benefits to users. Therefore, it is anticipated that adolescents will experience improvements in state-based body satisfaction and affect at the time of engagement with the chatbot.**H2**: Adolescents randomised into the intervention condition will experience greater improvements in trait-based body esteem, affect and body image self-efficacy at post-intervention, one-week and one-month follow-up, relative to the assessment only control condition.**H3:** Based on previous research into the moderating effects of gender [30] and trait psychopathology [31, 32] on body image intervention effectiveness, it was hypothesized that intervention effects will be moderated by gender, and baseline levels of body esteem, affect and body image self-efficacy. Specifically, intervention effects will be greatest among: girls; girls and boys with lower levels of trait body esteem; girls and boys with higher levels of trait negative affect and body image self-efficacy.**H4**: With regards to user engagement and adherence, given the novelty of this intervention, analyses will be of an exploratory nature. It is, however, anticipated that greater engagement and adherence with the chatbot intervention will lead to greater improvements in trait-based outcomes.

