### Data analyses

At trial completion, Toluna and Talk2U will deliver password protected datafiles to the corresponding author who will clean, screen and separate state- and trait-based data for blinding purposes. Data will then be delivered to the data analysts. Analyses will be conducted in Stata. A series of linear mixed effects models will test hypotheses. H1 analyses will be limited to intervention arm participants as there is no comparable pre- and post-technique data for the assessment-only arm, while analyses for H2, H3 and H4 will include participants from both study arms.

To test H1, the immediate effects of intervention content on state-based outcomes will be explored by regressing state-based outcome measures (body satisfaction and affect) onto a time variable (0 = pre-content, 1 = post-content). For H2-H4, scores on trait-level outcome variables will be regressed onto a dummy coded time variable, with baseline as the reference category compared against post-intervention, one-week, and one-month follow-up timepoints, using random effects to allow for individual differences in amount of change in symptoms over time. Group (control = 0, intervention = 1) will be included as a cross-level moderator to test group differences in change over time (H2). The moderating effect of baseline variables on this group effect will be conducted to test H3. In evaluating H4, adherence and engagement measures will be tested as moderators of change in trait-based outcome measures over time (relative to baseline) for intervention participants. Relations among random effects of Level 1 time variables will be modelled with an unstructured covariance matrix.

Baseline differences between intervention and control participants in terms of demographic factors will be tested. Any variables shown to differ across groups will be included as covariates in analyses. Linear mixed model results will be presented in adjusted and unadjusted forms to demonstrate impact of these covariates on results.

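### Chatbot use is encouraged beyond 72 hours but engagement is planned to be assessed only within them, so T3/T4 effects cannot be read as persistence of a 72-hour exposure, and H4 at T3/T4 reflects early engagement only

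*Protocol article*

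**What the plan says.** The section on the current trial design sets the exposure: "Participants in the intervention condition will interact with the chatbot over a 72-h period". The abstract says the same. T2 is placed at the end of this period and called post-intervention; T3 (one week) and T4 (one month) are called follow-up.

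The section on participant recruitment and procedure then adds, for the time after T2: "Those in the intervention condition will be encouraged to continue using the chatbot". No end to this is given. Under the same heading, controls receive the link only once every assessment is complete. The prompts for non-engagement are described only within the 72 hours.

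In Table 3 (Measures), the timing entry for intervention adherence is "72-Hour Intervention Period". Two of the listed metrics repeat the limit in their own wording. Completion is illustrated as a "minimum of 1 technique completed over the 72-h intervention period", and the total-time metric is "Average length of time spent engaging with the chatbot over the 72-h period". No section plans to measure use between T2 and T4.

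For H4, the data analyses section states that "adherence and engagement measures will be tested as moderators of change in trait-based outcome measures over time", within the intervention arm. The time coding it gives for H2 to H4 compares T2, one week and one month each with baseline. H4 is called exploratory but carries a directional expectation that "greater engagement and adherence with the chatbot intervention will lead to greater improvements in trait-based outcomes".

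**The concern.** Two statements do not fit together. The intervention is described as lasting 72 hours with follow-up afterwards, yet exposure may continue, with encouragement and in one arm only, up to both follow-up visits. The engagement data planned for analysis end where that continued exposure begins.

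Two readings are at stake:

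- **H2 at T3 and T4.** A difference between arms at one month could come from lasting benefit of the first 72 hours, from techniques done in the following weeks, or from both. The planned data cannot separate these. Trait body esteem, a primary outcome, is measured at these visits.
- **H4 at T3 and T4.** Someone who finishes one technique in 72 hours and several more afterwards enters the model as a low engager. The moderator is then early engagement, while the hypothesis speaks of engagement with the intervention in general.

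Later first exposure is plausible. A completer need have finished only one of the eight techniques, and techniques unlock in sequence within a theme, so new content may remain at T2.

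**Working it through.** **1. The plan's own figure.** The power section gives 1050 for the hypotheses confined to the intervention arm: 2800 / 2 = 1400, and 1400 × (1 − 0.25) = 1050. This reproduces. The point disputes no stated figure.

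**2. The planned window against time open to use.** Inputs: 72 hours = 3 days; T3 at 7 days and T4 at one month, taken as 30 days (assumption). The text does not fix the origin for follow-up, so both are shown.

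| Follow-up counted from | Share covered by T3 | Share covered by T4 |
|---|---|---|
| End of the 72 hours | 3 / (3 + 7) = 30% | 3 / (3 + 30) = 9% |
| Start of access | 3 / 7 = 43% | 3 / 30 = 10% |

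These are shares of calendar time, not of dose. Use may be concentrated in the first days.

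**3. How far H4 could be distorted.** Let E be use within 72 hours (SD 1) and L later use up to the visit (SD k), with correlation ρ between them. Suppose change depends on E + L, all use counting equally. Then:

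- corr(E, E + L) = (1 + ρk) / √(1 + k² + 2ρk)
- slope per unit of E, relative to the true slope = 1 + ρk

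The documents give neither k nor ρ; both are assumptions. Each cell shows the correlation, then the slope factor.

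| k | ρ = 0 | ρ = .3 | ρ = .6 |
|---|---|---|---|
| 0 (no later use) | 1.00; 1.0 | 1.00; 1.0 | 1.00; 1.0 |
| 0.5 | .89; 1.0 | .92; 1.15 | .96; 1.3 |
| 1 | .71; 1.0 | .81; 1.3 | .89; 1.6 |
| 2 | .45; 1.0 | .64; 1.6 | .81; 2.2 |

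The result runs from no distortion at all to a moderator that correlates below .5 with total use, or a per-technique slope more than doubled. Strong attenuation and strong slope inflation do not occur together: the first needs low ρ, the second high ρ.

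**4. Power for H4.** This is a rough check with the Fisher z approximation, two-sided alpha .05 and n = 1050. It takes the plan's r = .2 as the relation of change to cumulative use, which is an assumption. Power = Φ(atanh(r) × √1047 − 1.96).

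- k = 1, ρ = 0: r = .2 × .707 = .141, power above .99.
- k = 2, ρ = 0: r = .2 × .447 = .089, power about .83.
- Correlation of only .3 with cumulative use: r = .06, power about .49.

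Power suffers seriously only where 72-hour use is a very poor proxy. The main effect is on interpretation.

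**The case against.** The strongest reply is that the protocol claims less than the concern assumes. H2 predicts greater improvement than in controls at each visit, and the stated aim is immediate and short-term impact. The analysis is by intention to treat, and the comparison is framed as a real-world one against usual care. Randomised access with encouraged use against no access is a sound contrast at one month. This stands. A reader might infer that H2 at T3/T4 is biased or invalid, or that the protocol promises durability of a 72-hour effect. The documents support neither: the contrast follows randomisation, and no explicit durability claim is made.

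A reader might also infer that the platform stops logging at 72 hours. Table 3 does not say so. It gives the window in which adherence is to be assessed and introduces its metrics as a non-exhaustive list. The SPIRIT schedule is a figure not available here. What stands is that the text plans no use of later data.

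On H4, the analysis is called exploratory and T2 is unaffected. Engagement in a fixed early window is also a legitimate predictor that precedes the T3 and T4 outcomes. Cumulative use is no clean replacement: use after T2 may be driven by how the participant already felt, which brings reverse causation into the dose-response. This stands too, and is why cumulative use belongs in a sensitivity analysis.

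Finally, any single attenuation figure rests on assumptions about later use that the documents cannot support. The figures above show only a range. None of this reconciles the 72-hour definition, the encouragement after T2, the Table 3 window and the H4 model.

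**Conclusion.** The concern holds in a limited form. At T3 and T4, H2 estimates the effect of 72 hours of prompted use plus encouraged continued access, compared with no access. That estimate is valid, but it does not show that a 72-hour exposure persists. H4 at T3 and T4 relates change to early engagement, not to total dose; H4 at T2 is sound on this point.

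The firm quantity is the coverage of calendar time: 30–43% by T3 and 9–10% by T4, depending on the origin of follow-up and a 30-day month. The distortion of H4 is unknown, since it depends on the amount of later use and its correlation with early use. It is nil if little use follows T2. The point affects interpretation and does not undermine the primary randomised comparison. It is worth correcting because it is cheap and because an analysis plan cannot recover use that was never captured or exported.

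**What to change.** 1. Extend the export of the automatic engagement log for the intervention arm to T4, amend the timing entry in Table 3, and report use after 72 hours by visit.
2. Keep 72-hour engagement as the main H4 moderator and label it early engagement. Add cumulative use up to T3 and up to T4 as a sensitivity analysis, noting that later use may itself be driven by earlier outcome.
3. Describe the T3 and T4 contrasts as the effect of 72 hours of prompted use plus continued access.
4. If later use cannot be exported, limit H4 dose-response conclusions to T2 and say so.
5. Reconcile the current trial design, participant procedure, Table 3 and data analyses sections on what the exposure period is. Whether continued use should be encouraged is for the sponsor; the request is that it be measured and described.

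The cost is small: a longer export from the technology partner, which already delivers data files, a few changed sentences, and possibly consent wording to cover the longer period, which could not be checked here.

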### Randomisation and blinding

In the present trial, adolescents will be randomised to one of two conditions based on a permuted block design, using survey software by the research agency. Randomisation will be performed on an individual level to ensure timely allocation, while maintaining a balance of participants across conditions. Participants cannot be blinded to allocation due to the behavioural nature of the two conditions; however, they will be blinded to the study aims and hypotheses. As randomisation is conducted by an external research agency, researchers will be blinded to participant allocation. Data analysts will be blinded to condition allocation (dummy coded) when conducting statistical analyses on primary and secondary trait outcomes; however, blind analyses cannot be conducted on primary and secondary state measures due to the within-group design. State and trait data will be separated into two data files to ensure blinding is maintained for trait-based measures.

